### Monitoring intervention integrity

To keep track on the degree to which The COACH Program is delivered as initially planned and to monitor the compliance of the patients and their GPs to the advice of the coaches, the following measures are foreseen: 1) all written coaching reports are reviewed by IO and the head nurse during the first two months of the intervention and selectively thereafter; 2) several coaching sessions are audio-recorded; 3) the coaches register patient’s and GP’s compliance to their advice, particularly in adjusting medication therapy.

### Cost-utility analysis

Cost-utility analysis will be performed if the clinical study demonstrates a positive difference in clinical end points between two study groups [28,29]. Within-trial and modeled cost-utility analyses will be undertaken from the perspective of the health care system, i.e. taking into account direct health care costs to the system including both the cost for the health insurance as the patient out-of pocket costs [30].

The incremental cost-effectiveness ratio (ICER) will be calculated by using the following equation: ICER = ∆Costs/∆QALYs, where ∆Costs is the difference between the mean total cost in the intervention and the control group and ∆QALY is the area between two curves depicting the evolution of the means in QALYs-utilities over time in the intervention and the control group.

Modeling will be applied for projecting effects observed within the trial over a life-time horizon. The assumptions on the progression of type 2 diabetes depending on the known intermediate surrogate outcomes and the associated health status will be derived from published sources. The model’s outcomes validity will be tested through critical appraisal by experts. Future costs of type 2 diabetes without complications, and costs associated with each fatal or non-fatal diabetes-related complication will be estimated based on the epidemiological data available in Belgium and the database of the Independent Sickness Funds. Future costs will be discounted at 3%, future QALYs gained at 1.5% per annum [30]. ICERs will be calculated at various time horizons (e.g., 2, 5, 10, 20 years) [30].

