“The COACH Program” is a well-established target-driven telephone intervention delivered by nurses or dieticians who undergo special additional training [20]. It showed to effectively reduce the disease related risk factors in patients with established coronary heart disease after hospitalization [21,22]. After a research phase, The COACH Program became operational in Australia and extended its curriculum to ten different chronic conditions including type 2 diabetes, in the past 15 years. The clinical and cost-effectiveness of The COACH Program has not yet been tested in Europe.

The specific aims of the study are: 1) to assess whether The COACH Program can be offered by a sickness fund and delivered in cooperation with caregivers in Belgium; 2) to investigate whether The COACH Program helps people with type 2 diabetes to achieve better glycemic control and improved modifiable diabetes risk factors and self-perceived health compared with usual care alone; 3) to analyze the cost-effectiveness of The COACH Program from the perspective of the health care system based on the trial results extrapolated to a life-long horizon.

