## Methods/Design

### Study design

The study is a parallel-group RCT, in which patients with type 2 diabetes, affiliated to the Belgian sickness fund Partena, were selected based on their medication consumption data, recruited by their sickness fund, and randomized to receive usual care plus The COACH Program or the usual care alone. The study will assess the difference in outcomes between the two groups. The primary outcome measure is the level of glycohemoglobin HbA1c at 6 months after randomization. The secondary outcomes are: total cholesterol (TC), low-density lipoprotein (LDL), high-density lipoprotein (HDL), triglycerides (TG), blood pressure (BP), Body Mass Index (BMI), smoking status; proportion of people at target for HbA1c, LDL-Cholesterol and Blood Pressure; self-perceived health status, diabetes-specific emotional distress, and satisfaction with diabetes care. The follow-up period is 18 months. All outcome measurements will be collected 3 times: before randomization, upon the graduation from the program (6 months after the program start); and at the end of the follow-up period (18 months after randomization). The allocation ratio is 1:1. Within-trial and modeled cost-utility analyses, - to project effects over a longer time horizon beyond the trial duration, - will be undertaken from the perspective of the health care system if the intervention is effective.

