### Sample size

Sample size calculation was performed by using the stata software. For the subgroup of people with HbA1c ≥ 7%: assuming the difference of 0.4% between the control and intervention group (7.8% vs 7.4%) [4] and the standard deviation of 0.94% as observed within this subgroup at the baseline data analysis, we would need 232 people in both arms to achieve a power of 0.90 in this subgroup. 46% of the participants represent this group. This means that recruiting 555 people in total would be enough to power our hypothesis for the subgroup of people with HbA1c ≥ 7% at baseline if accounting for up to 10% drop-out.

For the total study population: based on the assumption that the mean difference in HbA1c between two groups will be of 0.3% (7.0% vs 6.7%) [2], and standard deviation of 1.05% - as analyzed at baseline – to achieve a power of 0.90 with alpha being 0.05, we would require 514 subjects to complete the study. Allowing for a dropout rate of up to 10%, the target recruitment number should be 566 patients totally, or 283 patients in each arm [27].

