## Discussion

Local context can have impact on the acceptability of new forms of care and on their clinical- and cost-effectiveness. Telephone coaching has been applied for patient education in USA and Australia since 1990-ties and has a potential to increase access to health care services. However, in systematic reviews on telehealth in chronic disease management, European studies are poorly represented [13,14,20]. It is therefore important to investigate the transferability of successful telehealth interventions to European countries through studies of a high methodological quality. To increase the added value of such research to patients and policy makers, study designs have to consider the clinical effectiveness, the cost-effectiveness and the implementation potential.

The design of our study has several strengths. 1) The intervention integrity analysis is integrated into the study protocol. The verification of program integrity should be part of the evaluation of any behavioural intervention as lowered adherence to the protocol is often associated with poorer outcome [31]. The integrity assessment also reveals important information about the feasibility of the intervention in real life settings. 2) The COACH Program is well-established in Australia, which enables a comparison of the clinical outcomes in relation to the integrity results. 3) Patients were invited into the study directly, reducing the potential of selection bias. 4) The cost-effectiveness analysis with life-time horizon will help the policy makers to prepare well informed reimbursement decisions. 5) The database of the sickness funds is a reliable and comprehensive source of information on health care consumption.

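### The cost-utility analysis is conditional on a favourable clinical result, but the third aim promises it without condition and may go unanswered

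*Protocol article*

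**What the plan says.** The condition appears three times in the protocol article. The Cost-utility analysis section gives it as "Cost-utility analysis will be performed if the clinical study demonstrates a positive difference in clinical end points between two study groups". Study design says that the within-trial and modelled analyses "will be undertaken from the perspective of the health care system if the intervention is effective", and the Methods/Design part of the Abstract repeats this. No section describes an economic analysis for the case where the condition is not met.

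Two other places carry no condition. The third aim in the Background, which looks to a lifelong horizon, is "to analyze the cost-effectiveness of The COACH Program from the perspective of the health care system based on the trial results". The Discussion counts the economic work among the strengths of the design: "The cost-effectiveness analysis with life-time horizon will help the policy makers to prepare well informed reimbursement decisions".

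The quantity to be estimated is "ICER = ∆Costs/∆QALYs". The section on within-trial costs and health utilities takes the utilities from EQ-5D and service use from the sickness funds' database. For the longer horizon, "Modeling will be applied for projecting effects observed within the trial over a life-time horizon".

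**The concern.** A stated aim of the trial is made optional elsewhere in the same article. The condition also rests on a different quantity from the one to be estimated. A clinical end point such as HbA1c enters neither the cost term nor the EQ-5D term of the within-trial ratio. A coaching programme can change service use, medication cost or utility without a demonstrable clinical difference, and it has its own delivery cost in any event. A null clinical result therefore does not tell a payer whether the programme is worth funding, and that is the question the trial says it will help to answer.

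There is a second, smaller consequence. If the lifetime model is run only after a favourable clinical result, the clinical effect that it projects has been selected for being large.

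**Working it through.** **1. The passages side by side.**

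| Place | Is the economic analysis conditional? |
|---|---|
| Abstract, Methods/Design | Yes, on effectiveness; within-trial and modelled |
| Study design | Yes, on effectiveness; within-trial and modelled |
| Cost-utility analysis | Yes, on a favourable clinical difference |
| Background, third aim | No |
| Discussion, strengths | No |

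**2. Are the data there if the clinical result is null?** Table 1 schedules EQ-5D and costs at baseline, 6 months and 18 months. The only item it restricts to the intervention group is satisfaction with the programme. The section on costs of the intervention registers those costs prospectively. The inputs to the within-trial ratio therefore exist in both arms whatever the clinical result.

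**3. The plan's own sample size.** The Sample size section gives a difference of 0.3, SD 1.05, alpha 0.05, power 0.90 and 514 completers; Statistical analysis gives a two-tailed test; allocation is 1:1.

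n per arm = 2 × (1.960 + 1.2816)² × 1.05² / 0.3² = 257.4. This is 258 when rounded up, or 516 in total. The stated 514 is 2 × 257, so the figure is reproduced to within rounding.

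**4. How often the condition would fail.** The article does not say what counts as *positive*. Assume first that it means p<0.05 in favour of coaching on the primary outcome ("The primary outcome measure is the level of glycohemoglobin HbA1c at 6 months after randomization"). Let d be the true difference and SE the standard error of its estimate.

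SE = 1.05 × √(4/514) = 0.0926.

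P(not done) = Φ(1.96 − d/SE).

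- d = 0.3: Φ(1.96 − 3.24) = 0.10
- d = 0.2: Φ(1.96 − 2.16) = 0.42

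The value 0.3 is the design difference. The value 0.2 is an assumption; the article gives no smaller effect.

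**5. Selection of the HbA1c effect.** With a = 1.96 − d/SE, the mean estimate when the condition is met is d + SE × φ(a) / (1 − Φ(a)).

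- d = 0.3: 0.318, or 0.318/0.3 = 1.06 times the truth
- d = 0.2: 0.263, or 0.263/0.2 = 1.31 times the truth

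**6. The weaker reading.** If a favourable sign is enough, replace 1.96 by 0.

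- d = 0.3: not done in about 0.1%; mean estimate 0.300
- d = 0.2: not done in about 1.5%; mean estimate 0.204, or 1.02 times the truth

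**7. Sensitivity to numbers.** If all 574 patients assessed at baseline were analysed, step 4 gives 7% and 37%, and step 5 gives ratios of 1.04 and 1.27.

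**The case against.** The condition is declared in advance, is stated consistently in three places and cites methodological sources. Not building a lifetime model for a programme without a demonstrated effect can be a sensible use of resources. At the design difference the 10% is simply the planned type II error, and the 6% is small. All of this stands, and it is why a conditional lifetime model can be acceptable. It does not reconcile the condition with an aim worded without it, and it gives no reason to withhold the within-trial analysis.

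A reader might infer more than the article supports, in four ways.

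- **That the ICER itself is inflated by these ratios.** They apply to HbA1c. Selection on HbA1c moves the within-trial ratio only as far as cost and EQ-5D differences go along with HbA1c, and nothing in the article measures that. The Discussion suggests that EQ-5D may respond weakly to small changes.
- **That an unfavourable ICER would be withheld.** The condition is on the clinical result. Once it is met, a poor ICER would still be calculated.
- **That any one of the many listed outcomes could trigger the analysis.** The end points are in the plural, but no section says that one is enough. There is a single primary outcome, and two of the three statements refer simply to effectiveness. The exact criterion may also stand in a fuller document that is not shown.
- **That the model would take only significant effects.** Nothing says so. Statistical analysis plans probabilistic sensitivity analysis for all model inputs.

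**Conclusion.** The point holds as an internal contradiction with a practical consequence: the plan can be followed exactly and still leave its third aim unanswered, although the data to address it would be in hand. This conclusion needs no numerical assumption.

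The size does depend on assumptions. With the condition read as p<0.05 on HbA1c, SD 1.05 and 514 completers, the economic analysis is not done in about 10% of trials at a true difference of 0.3 and in 42% at an assumed 0.2. The HbA1c effect projected by the lifetime model is overstated by about 6% and 31% on average. If a favourable sign is enough, both problems are negligible at these effects. The primary HbA1c analysis is not affected under any reading.

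**What to change.** Remove the condition for the within-trial cost-utility analysis in the Abstract, Study design and Cost-utility analysis. State there that it will be performed and reported whatever the clinical result. Present the joint uncertainty in costs and QALYs with the methods that Statistical analysis already plans, namely the cost-effectiveness plane and the acceptability curve.

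If the sponsor wishes to keep the lifetime model conditional, tie that condition to the primary endpoint, HbA1c at 6 months, with a stated criterion. The third aim must then be reworded to match, because it names the lifelong horizon: it should promise the within-trial analysis outright and the extrapolation only if the criterion is met. The Discussion should follow.

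The cost is some additional health-economic analysis if the clinical result is null. No new data are needed, and the sample size and primary analysis stay as they are.

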### Costs of the intervention

The fixed intervention costs consist of the investment into the program development, the administrative and supporting personnel, the software maintenance, the consultancy services, and the overhead. Variable costs are those costs which are directly dependent on the number of patients served by the program and associated with the training of the coaches, the recruitment of patients into the program, the actual coaching and administration time, once-off per patient fee, and production and distribution of the program materials for coaches and patients. All costs will be registered prospectively during the trial based on the individual time and material registration and the contractual prices. Fixed costs will be allocated to patients through dividing the total fixed costs by the number of participants in the intervention group.

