**Figure 1 F1:**
[figure not shown]
RCT flowchart including the numbers of the enrolled and randomized patients.

**Table 2 T2:** Baseline clinical characteristics of patients in the COACH program and usual care groups

**Characteristic**	**The COACH program (n = 287)**	**Usual care (n = 287)**
Sex, no (%)		
Male	173 (60)	180 (63)
Female	114 (40)	107 (37)
Age, years		
Mean (SD)	63.8 (8.7)	62.4 (8.9)
Median (range)	65.9 (35–75)	63.9 (35–75)
HbA1c, % (mmol/mol)	7.0 (53)	7.0 (53)
Mean SD	1.1 (12)	1.0 (11)
Total cholesterol, mg/dl mean (SD)	173 (37)	178 (39)
LDL-C, mg/dl mean (SD)	93 (31)	97 (32)
HDL-C, mg/dl mean (SD)	52 (19)	51 (14)
Triglyceride, mg/dl median (range)	127 (42–1369)	130 (35–1993)
Systolic blood pressure, mmHg mean (SD)	133 (18)	132 (17)
Diastolic blood pressure, mmHg mean (SD)	75 (10)	76 (10)
BMI (kg/m2) mean (SD)	30 (5)	31 (5)
People at treatment target, no (%)		
HbA1c < 7% (53 mmol/mol)	155 (54)	159 (55)
LDL-C < 100 mg/dl	172 (60)	164 (57)
SBP < 140 mmHg	174 (61)	186 (65)
DBP < 80 mmHg	160 (56)	160 (56)
At target for all above risk factors	40 (14)	46 (16)
BMI < 25 kg/m2	33 (11)	28 (10)
In the subgroup with HbA1c ≥ 7% (53 mmol/mol)		
HbA1c, % (mmol/mol)	7.9 (63)	7.8 (62)
MeanSD	1.0 (11)	0.8 (9)
*Self-reported*		
Diagnose type 2 diabetes since, no (%)		
≤ 2 years	46 (16)	41 (14)
≥ 10 years	94 (33)	91 (32)
Smokers, no (%)	40 (14)	54 (19)
People with 1st grade relatives with known type 2 diabetes, no (%)	159 (56)	139 (49)
People with 1st grade relatives with cardiovascular disease diagnosis before 60 y.o., no (%)	93 (33)	90 (32)
With regular hypoglycemia, no (%)	26 (9)	36 (13)
People with other chronic condition(s), no (%)	211 (74)	217 (76)
Coronary heart disease	35 (12)	39 (14)
Atherosclerosis	19 (7)	9 (3)
Heart failure	21 (7)	14 (5)
Past MI	11 (4)	14 (5)
Past stroke	11 (4)	4 (1)
Past TIA	8 (3)	5 (2)
COPD	11 (4)	15 (5)
Asthma	13 (5)	19 (7)
Hypertension	111 (39)	113 (39)
Dyslipidemia	81 (28)	80 (28)
Kidney disease	17 (6)	10 (3)
Depression	19 (7)	24 (8)
Neuropathy	10 (3)	16 (6)
Having physical activity* of 30 minutes at least 5 days per week, no (%)	170 (59)	159 (55)
Having daily healthy diet**, no (%)	181 (63)	157 (55)

*Physical activity is moderate aerobic activity at 50–70% of maximum heart rate (1).

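### The only fixed-cost rule divides by the 287 intervention-arm participants, so an ICER meant for reimbursement depends on trial size unless a roll-out scenario is added

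*Protocol article*

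**What the plan says.** The section Costs of the intervention in the protocol article defines the fixed part: "The fixed intervention costs consist of the investment into the program development, the administrative and supporting personnel, the software maintenance, the consultancy services", together with overhead. Variable costs are those that move with the number of patients served. The same section then fixes the allocation: "Fixed costs will be allocated to patients through dividing the total fixed costs by the number of participants in the intervention group". On data capture it says: "All costs will be registered prospectively during the trial based on the individual time and material registration and the contractual prices".

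The Cost-utility analysis section plans a within-trial and a modelled analysis, both from the health care system's perspective and only if the trial is clinically positive. It defines the numerator of the ICER: "where ∆Costs is the difference between the mean total cost in the intervention and the control group". Its modelling paragraph covers projected effects and the future costs of diabetes and its complications. It does not say which intervention cost enters the model.

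Within trial costs and health utilities analysis leaves out costs that the study imposes and that are not routine practice. The Discussion states the purpose: "The cost-effectiveness analysis with life-time horizon will help the policy makers to prepare well informed reimbursement decisions".

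**The concern.** A fixed cost, by the article's own definition, does not depend on how many patients are served. Its value per patient therefore has meaning only once a programme scale is stated. The scale used here is the size of one trial arm, which follows from the HbA1c sample size and from the design ("The allocation ratio is 1:1"). Neither says how many people a sickness fund would serve or how long the development investment would last.

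This sits badly with two of the article's own aims. The costing removes study-imposed costs in order to reflect routine delivery, yet the fixed-cost denominator is itself a product of the study. And the lifetime analysis is meant to inform reimbursement, where the question is what a running programme costs per patient. At stake is whether a programme that proves clinically effective looks less cost-effective than it would be in routine use.

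**Working it through.** The article gives no fixed-cost total, cost per patient or ICER, so there is no stated figure to reproduce. The check shows how the result depends on the denominator.

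**Inputs from the article**
- Intervention arm: 287; usual care: 287 (Table 2).
- Eligible people who took part in the baseline assessment: 574 (Patient recruitment and baseline data). This equals 287 + 287.

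**Assumptions**
- Fixed-cost total F: EUR 100,000 to 500,000.
- QALY difference: 0.01 to 0.05.
- Share d of F that is development cost, the remainder being recurrent.

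**Step 1: how F enters the ICER.** Usual-care patients receive no programme, so the whole of F/N enters the cost difference. The fixed-cost part of the ICER is (F/N)/∆QALY.

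**Step 2: cost per patient if F does not change with N.**

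| F (EUR) | N = 287 | N = 574 |
|---|---|---|
| 100,000 | 348 | 174 |
| 250,000 | 871 | 436 |
| 500,000 | 1,742 | 871 |

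The ratio 287/574 = 0.5 holds for any F. Had everyone eligible in this one recruitment round been offered the programme, the charge would be half. The doubling comes from randomising half of them to usual care.

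**Step 3: the fixed-cost part of the ICER for F = EUR 100,000.**

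| ∆QALY | N = 287 | N = 574 |
|---|---|---|
| 0.01 | about 34,800 | about 17,400 |
| 0.02 | about 17,400 | about 8,700 |
| 0.05 | about 7,000 | about 3,500 |

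Units are EUR per QALY. The absolute values depend entirely on the assumed F and ∆QALY.

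**Step 4: recurrent costs do not stay constant.** Support staff, software maintenance, consultancy and overhead continue for as long as the programme runs and may grow with it. At the opposite extreme from Step 2, let the recurrent part grow in proportion to caseload. Cost per patient is then F × [d/N + (1 − d)/287]. With F = EUR 100,000, N = 574 and d = 0.5:

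100,000 × (0.5/574 + 0.5/287) = 87 + 174 = EUR 261.

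For d = 0.5 at a caseload of 574, the charge therefore lies between EUR 174 (no growth) and EUR 261 (proportional growth), against EUR 348 under the stated rule. Larger caseloads lower the development part further.

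**Step 5: would the planned uncertainty analyses show this?** F/287 is the same constant for every intervention patient, so it adds nothing to the confidence limits of the cost difference. The Statistical analysis section plans one-way, probabilistic and structural analyses. These could carry a change of scale, but neither programme scale nor fixed-cost allocation is named among them.

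**The case against.** The strongest reply is that F/287 is correct for the within-trial analysis: it is what the trial spent per treated patient. Aim 3 is worded as an extrapolation of the trial results, and an observed denominator is safer than an invented caseload. All of this stands, and it is why the 287-patient figure should be kept.

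A reader might infer that the article commits the lifetime model to the 287-patient figure. It does not say so. The supported statement is narrower: no other intervention cost or allocation rule is given for that model.

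A reader might also infer that the whole development outlay is loaded onto this one cohort. That too is uncertain. The programme was already running in Australia, and costs are registered prospectively during the trial, so earlier spending may fall partly outside F.

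Nor does the article say that QALY gains are expected to be small. The Discussion speaks of the limited capacity of generic surveys to detect minor differences, which concerns the instrument.

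The planned sensitivity analyses could absorb the issue, and a condensed article may leave amortisation details to a fuller document. That absence is not the point here. The point is the rule the article does state, without limiting it to the within-trial account.

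Finally, the document offers no firm roll-out caseload. The 685 who agreed include people who were not eligible. The share of those invited who took part is 574/3,115 = 18%, and it describes existing patients recruited between April 2012 and June 2013, not a yearly flow. This argues against replacing the base case with a single assumed caseload.

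**Conclusion.** The point holds as a modest improvement to the economic analysis. The stated rule is sound for trial-scale spending. As the only rule for an ICER aimed at reimbursement, it ties the fixed-cost part to arm size and allocation ratio. The direction is known: cost per patient is overstated, and the programme looks less cost-effective, if more than 287 people are served. The size is not known, because F, its split between development and recurrent cost, and the eventual caseload are not given. The EUR figures above are illustrations and not estimates of bias. A stronger conclusion, that the ICER would be invalid or relevant only to an unrealistic setting, is not supported. The primary HbA1c analysis is unaffected, and the issue arises only if the cost-utility analysis goes ahead.

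**What to change.** - Keep division by 287 and label it the within-trial, trial-scale result.
- For the modelled analysis, prespecify a roll-out scenario. Separate development investment from recurrent fixed cost, spread the development part over a stated useful life and expected caseload, and scale the recurrent part to that caseload.
- State whether development spending from before the trial is included in the fixed-cost total.
- Name caseload and useful life as variables in the planned tornado diagram and scenario analyses.

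The cost is a few sentences and a short recalculation, provided the cost records allow development and recurrent items to be separated. The downside is that caseload and useful life are assumptions. They should be reported as a range beside the trial-scale figure, not as a single replacement base case.
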